### Study Procedures

#### Recruitment and Informed Consent

Participants will be recruited from the inpatient behavioral health units located in Lubbock, Texas. The inclusion criteria are as follows: (1) current inpatient behavioral health treatment, (2) aged at least 18 years (no maximum age), and (3) SI or suicidal behavior in the week before admission. The exclusion criteria are as follows: inability to complete tasks because of (1) impaired mental status (orientation score <5 on the Montreal Cognitive Assessment), (2) acute psychotic or manic symptoms, or (3) low English fluency. Treatment team members (eg, attending physicians and nursing staff) will identify individuals who are potentially eligible for the study and ask these individuals for verbal consent to be approached by a team member regarding the study. Informational flyers describing the study will be provided to treatment team members to offer to interested patients; team members will also be provided scripts to describe the study orally. With approval, a study team member will then approach potential participants during times that do not conflict with treatment or unit activities to discuss the study. The study team member will meet with the potential participant in a private area on the unit to explain the study design, procedures, risks and benefits, compensation, confidentiality and its limits, and eligibility criteria. Oral and written consent will be obtained from participants before proceeding. Study consent forms, the prescreening form, and summary information sheets are available alongside the Open Science Framework preregistration [89]. A diagram showing the flow of potential participants through study procedures is presented in Figure 2.

**Figure 2 figure2:**
[figure not shown]
Study recruitment, enrollment, and procedures flow chart. EMA: ecological momentary assessment; MoCA: Montreal Cognitive Assessment; STB: suicidal thoughts and behaviors.

#### Baseline Session

The baseline session will take place on the inpatient behavioral health unit and last for 2 to 3 hours. Participants will complete self-report surveys, clinical interviews, a computer task (Emotional Stop-Signal Task), and a debriefing procedure. Participants will also be instructed on how to complete the follow-up EMA surveys and mobile computer tasks, as well as how to use the actigraphy device. A complete list of self-report measures and clinical interview assessments is provided in Table 1. A summary of study data collection procedures as well as all baseline measures are provided alongside the Open Science Framework preregistration [89].

**Table 1 table1:** Self-report and clinical interview measures for the baseline session.

Measure type and construct			Measure
**Self-report**			
	Age, race, ethnicity, gender, and other demographics	Demographics	
	Positive and negative affect	Positive and Negative Affect Schedule	
	Emotion-related impulsivity	Three-Factor Impulsivity Scale	
	Thwarted belongingness	Interpersonal Needs Questionnaire	
	Perceived burdensomeness	Interpersonal Needs Questionnaire	
	Defeat	Defeat Scale	
	Entrapment	Entrapment Scale	
	Hopelessness	Beck Hopelessness Scale (4-item version)	
	Emotional pain	Psychache Scale	
	Physical pain interference	PROMIS^a^ Pain Interference Scale	
	Sleep chronotype	Smith Morningness-Eveningness Scale	
	Severity of insomnia	Insomnia Severity Index	
	Symptoms of sleep disorders	Sleep Disorders Symptoms Checklist-25	
	Coping strategies for suicidality	Suicide-Related Coping Scale	
	Exposure to traumatic events	List of Threatening Experiences Questionnaire	
	Recent depression, anxiety, and stress symptoms	Depression Anxiety Stress Scales (21-item version)	
	Capability for suicide	ACSS^b^ Fearlessness About Death Subscale	
	Access to lethal suicide means	PhenX^c^ Access to Lethal Means protocol	
	Onset and typical patterns of menstrual cycle	Menstrual history (women only)	
**Interview**			
	Past week suicidal ideation or behavior	Past Week Suicide Assessment	
	Lifetime, past year, past month, and past week suicidal ideation and behavior	Columbia Suicide Severity Rating Scale	
	Lifetime, past year, past month, and past week nonsuicidal self-injury urges and behaviors	Self-Injurious Thoughts and Behaviors Interview (NSSI^d^ items)	
	Lifetime and past year alcohol use disorder symptoms	Structured Clinical Interview for DSM-5^e^ Disorders (Alcohol Use Disorder items)	
	Lifetime and past year substance use disorder symptoms	Structured Clinical Interview for DSM-5 Disorders (Substance Use Disorder items)	
	Borderline personality disorder symptoms	Structured Interview for DSM-IV^f^ Personality Disorder (Borderline Personality Disorder items)	
	Current medications and dosages	Medication Interview	

^a^PROMIS: Patient-Reported Outcomes Measurement Information System.

^b^ACSS: Acquired Capability for Suicide Scale.

^c^PhenX: Phenotypes and Exposures.

^d^NSSI: nonsuicidal self-injury.

^e^DSM-5: Diagnostic and Statistical Manual of Mental Disorders, Fifth Edition.

^f^DSM-IV: Diagnostic and Statistical Manual of Mental Disorders, Fourth Edition.

Participants will complete an adapted version of the Emotional Stop-Signal Task [95] to behaviorally assess impulsivity. To focus on emotion-relevant response inhibition, we use an adapted version in which participants are presented with either neutral or negatively valenced images. In *Go* trials (75%), participants press a key to indicate the valence of the image within 1500 milliseconds. *Stop* trials (25%) involve a sound played through headphones at a variable delay after stimulus presentation and indicate that participants should inhibit their response to the image. The delay begins at 250 milliseconds and then increases or decreases by 50 milliseconds in response to successful or failed inhibitory control, respectively. The scores, then, reflect the difference in commission error rates between negative and neutral stimuli, which is an indicator of deficits in cognitive inhibition specific to negative affective contexts. During the baseline session, participants will complete practice trials followed by 3 blocks of 64 trials (192 trials, 48 *stop* trials).

#### Intensive Longitudinal Protocol

During the baseline session, participants will be asked to provide their typical wake times and bedtimes, as well as any specific windows of time in which they will be unavailable to answer surveys (for instance, work shifts in which they are not allowed to access their phone), which are then used to schedule the EMA survey distribution. Participants who do not own a mobile phone capable of accessing the internet will be provided with a *loaner* phone to use for the EMA surveys; other participants will use their own mobile phone. All participants will be walked through practice EMA items to familiarize them with the structure of the EMA surveys and the mobile version of the Emotional Stop-Signal Task before discharge.

The EMA surveys will be distributed using a proprietary distribution system that integrates with Amazon Web Services’ Simple Notification Service system to send SMS text messaging notifications of survey availability. These notifications will include a link to a Qualtrics survey that will be available for 30 minutes only after each notification.

Participants will receive 7 pseudorandom notifications between specified wake times and bedtimes, avoiding the blackout windows specified by the participant. We will add 15 minutes to the wake time to avoid missed surveys because of variability in wake times as well as to ensure that participants will be able to respond effectively to items regarding affect and related constructs after waking. Notifications will be randomized by *binning* the participants’ available hours into 7 equal windows and then randomly choosing a survey time within each bin. Notifications cannot occur within 30 minutes of another notification. If participants do not click the survey link within 10 minutes of notification, they will receive a reminder message. At each EMA prompt, participants will be asked to complete self-report items assessed using Qualtrics and then to complete the Emotional Stop-Signal Task on their mobile phone using the Inquisit web platform (Millisecond Software, LLC; available for both iOS and Android platforms). This adapted version of the task also uses negative and neutral stimuli. At the first survey completed each day, the task will have 128 trials (64 negative and 64 neutral trials interspersed). At each subsequent pseudorandom prompt, participants will complete 64 trials (32 negative and 32 neutral trials interspersed) to reduce participant burden while allowing within-person dynamic modeling of changes in affective inhibitory control. The domains assessed using EMA self-report items are listed in Table 2, and specific items are provided alongside the Open Science Framework preregistration [89].

**Table 2 table2:** Domains assessed using self-report ecological momentary assessment items.

Survey and construct		Number of items
**Morning survey only**		
	Sleep quality	1
	Sleep characteristics (time to bed, time to wake up, awakenings, and nightmares)	8
	Menstrual cycle (only for participants with regular menstrual cycle reported at baseline)	2
**All surveys**		
	Current suicidal ideation	2
	Current urges for nonsuicidal self-injury	2
	Current negative affect	6
	Current positive affect	2
	Current hopelessness	1
	Current agitation	2
	Current emotional pain	2
	Current defeat	2
	Current entrapment	2
	Current self-criticism	2
	Current suicide capability	4
	Current physical pain interference	1
	Current belongingness	2
	Current burdensomeness	2
	Current perceived emotional support	2
	Current perceived practical support	2
	Since last survey: suicidal behavior	1
	Since last survey: nonsuicidal self-injury	1
	Since last survey: stressors	3
	Since last survey: complimented or praised	1
	Since last survey: alcohol use	2
	Since last survey: drug use	4

At baseline, participants will also be provided with the actigraphy device (wActiSleep-BT; ActiGraph, LLC) and instructed on how to wear it during the follow-up period. Participants will be asked to wear the device as much as possible for 28 days after discharge. The device continuously records activity through accelerometer (approximately 30-hertz data sampling with timestamps) with a single charge typically exceeding 28 days [96]; however, participants will also be provided with a charger and asked to charge the device at least twice during follow-up at times when the watch would not otherwise be worn, such as when bathing. The device continuously records data to provide valid scores for a variety of indices, including sleep duration, sleep onset latency, total awakenings, length of awakenings, overall sleep efficiency, intensity of movement during sleep awakenings, and light exposure during sleep [97]. Participants will be provided with a self-addressed, postage-paid envelope to return the actigraphy device, charger, and loaner phone (if applicable) to the research team after study completion.

#### Follow-up Interviews

Participants will be asked to complete a brief remote (phone or videoconference) follow-up interview assessing STB at 4 weeks and 8 weeks after discharge, with the goal of ensuring that the follow-up data capture all experienced STBs even if not reported on the EMA surveys. Specific follow-up interview items are provided alongside the Open Science Framework preregistration [89].

#### Risk Assessment, Crisis Response Planning, and Strategies for Retention and Study Engagement

Participants who consent to participate in the EMA portion of the study will be contacted on a regular basis to identify concerns with the study, issues regarding receipt of the EMA notifications, and to assess ongoing suicide risk. All participants, regardless of their level of compliance with the EMA protocol and indicated suicide risk, will be contacted by the research team through SMS text messaging weekly (4 times over the 28-day period). Participants will also be contacted on day 5 of the EMA protocol if under half of the expected surveys are completed during the first 4 days of the protocol to remind them of the compensation rate per survey and to ascertain if any issues were inhibiting completion of the surveys. Participants will then be contacted if they demonstrate 1, 2, and 4 consecutive days of nonresponse to any surveys. After the first occurrence of extended periods of noncompletion, check-ins will only be conducted after 2 or 4 full days without completing any surveys to avoid excessive or intrusive follow-ups.

Participants will also be contacted within 24 hours of any EMA surveys in which they indicated engaging in suicidal behavior. These contacts will follow a specified risk assessment and crisis response plan dependent on participants’ responses and indicated level of imminent risk. The procedures used during these follow-ups are available in documentation alongside the Open Science Framework preregistration [89].

#### Compensation

Participants’ compensation will depend on the specific study components completed. Payments will be provided either through a digital Amazon gift card (by email) or a physical Walmart gift card (during face-to-face interactions or by mail). All participants who complete the informed consent process at baseline will receive a US $30 gift card, regardless of how many measures they complete.

All participants who consent to complete the EMA and actigraphy follow-up portion of the study will receive a US $50 gift card, regardless of the number of surveys completed or amount of time the actigraphy device is worn. Participants will receive an additional US $1 for each survey completed (up to an additional US $196). If participants complete at least 75% (147/196) of the surveys received, they will receive a bonus US $25 gift card. Participants will receive a US $20 gift card for completion of a follow-up interview, up to a maximum of US $40 for both the 4-week and 8-week follow-up assessments.

#### Data Analysis Plan

Before conducting analyses, we will clean and check data for errors, address outliers, ensure that statistical assumptions for analyses have been met, and examine potential confounders to include in subsequent analyses as warranted. Variables that may exhibit skewness (eg, number of lifetime episodes of NSSI) will be examined for skewness and kurtosis and, if necessary, either rank transformed or log transformed. We will include the effect of time (196 prompts over 28 days) to account for habituation and examine potential nonlinear effects of, for instance, age. Most analyses will use time-series (dynamic) structural equation modeling [98,99], which uses Bayesian estimation, conducted with MPlus statistical software (Muthén & Muthén) [99]. Dynamic structural equation modeling is robust with regard to high rates of missing data, zero-inflated categorical variables, and variable time intervals among observations, all of which are common in EMA with these types of data, and allows for latent decomposition of constructs into their constituent between- and within-person components [98]. Dynamic structural equation modeling also facilitates within-person lagged analyses to examine prospective relationships between time *t* predictors and time *t*+1 outcomes; by controlling for autoregressive effects over time, these methods can model within-person change in constructs over time.

For H1a, we will examine whether within-person changes in negative affective experiences precede proximal within-person changes in SI using 2-level random slope models. Each of 7 momentary negative affective experiences reported at time *t* will be regressed on itself at time *t–*1, producing a measure of residualized change in each negative affective experience. Momentary SI reported at time *t* will be regressed on itself at time *t–*1, as well as the 7 negative affective experience change indicators, yielding an estimate of the within-person effect of changes in all negative affective experiences on subsequent within-person changes in SI, controlling for autoregression. For H1b, we will examine the within- and between-person factor structures of the 7 negative affective experiences using multilevel exploratory factor analysis [100]. Using established best practices, we will identify the most appropriate structure and use these within-person factors to predict changes in SI over time, similar to the procedures used for H1a.

For H2a, we will estimate the effects of baseline emotion-related impulsivity and inhibitory control on odds of SA over follow-up, controlling for between-person differences in SI severity. To do this, person-mean estimates of SI and person-maximum estimates of SA (yes or no) will be calculated using EMA data. SA can then be predicted by baseline emotion-related impulsivity and inhibitory control scores using logistic regression analysis, controlling for participants’ SI severity. For H2b, we will then test whether within-person changes in state inhibitory control precede subsequent SA among individuals reporting SI. Using a 2-level random slope model, we will model time *t* inhibitory control (controlling for inhibitory control measured at time *t–*1) as a predictor of time *t*+1 SA, controlling for time *t* SI.

For sleep-related hypotheses, we will use 2-level random slope models, as described previously, but in which survey-level data on SI and SA have been pooled to create day-level variables (because sleep varies at the daily, but not survey, level). For H3a, we will use person-mean–centered total sleep time on day *d–*1 to predict next-day (day *d*) SI, controlling for day *d–*1 SI. Models for H3b will parallel those used to test H2a, whereby total sleep time on day *d*-1 will be used to predict next-day SA (day *d*), controlling for day *d* SI. For H3c, we will test whether the sleep-SA association (H3b) is mediated by within-person changes in inhibitory control. Building on the H3b model, we will add in the effect of sleep on day *d–*1 predicting inhibitory control on day *d*. To ensure that we are capturing sleep-related changes in inhibitory control, inhibitory control on day *d* will also be regressed on inhibitory control measured on day *d–*1. Finally, day *d* inhibitory control will be used to predict day *d* SA, controlling for day *d* SI. Indirect and direct effects will be calculated and tested for significance using the MPlus *model indirect* command.

With respect to the criteria used for statistical inferences, these will vary by model and hypothesis. For logistic regression analyses (H2a), 2-tailed *P* values <.05 will be used as our criteria to make inferences. For dynamic structural equation models (H1a, H1b, H2b, H3a, H3b, and H3c), which use Bayesian estimation, 95% credibility intervals will be used; those intervals that do not include 0 will be evidence of a statistically significant effect. For multilevel exploratory factor analysis (H1b), we will examine unrestricted models with 1 to 7 factors at the within- and between-person levels, consistent with the components of the negative affective experiences construct. We will determine the most appropriate model fit based on an examination of model fit indices [101] as well as eigenvalues.

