### Hypotheses

The goal of this study is to integrate examination of affective, cognitive, and physiological risk factors for short-term changes in suicidal thinking and suicidal behaviors among adults known to be at high risk within an ideation-to-action framework. To that end, our hypotheses are as follows:

Hypothesis 1a (H1a): within-person increases in affective suicide risk factors conceptually related to psychache (negative affective experiences) will individually precede within-person increases in SI.Hypothesis 1b (H1b): negative affective experiences will co-occur in daily life such that they are best conceptualized as indices of a single latent construct capturing emotional distress (psychache), which will itself predict short-term increases in SI.Hypothesis 2a (H2a): among those with SI, higher baseline self-reported emotion-related impulsivity will predict greater odds of SA over follow-up.Hypothesis 2b (H2b): among those with SI, poorer baseline behavioral indices of inhibitory control in the context of negative affective stimuli will predict greater odds of SA over follow-up. We also predict that, among those with current SI during EMA, lower EMA-assessed inhibitory control will prospectively predict subsequent SA.Hypothesis 3a (H3a): during the EMA protocol, short sleep duration will predict within-person increases in SI.Hypothesis 3b (H3b): during the EMA protocol, short sleep duration will predict greater risk of next-day SA among those with SI.Exploratory hypothesis 3c (H3c): the within-person effects of short sleep duration on SA will be mediated by within-person changes in inhibitory control assessed during EMA.

A visual depiction of these hypotheses is provided in Figure 1.

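### The H1a model, and H1b's prediction step, pairs affect and suicidal ideation from the same survey, so it cannot show that affect comes first

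*Protocol article*

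**What the plan says.** The Hypotheses section makes H1a a claim about order: increases in each negative affective experience "will individually precede within-person increases in SI". H1b adds a latent psychache factor, "which will itself predict short-term increases in SI".

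The Data Analysis Plan repeats the aim, asking "whether within-person changes in negative affective experiences precede proximal within-person changes in SI". It then sets out the model in two steps:

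1. "Each of 7 momentary negative affective experiences reported at time *t* will be regressed on itself at time *t–*1". The residual serves as the change indicator.
2. "Momentary SI reported at time *t* will be regressed on itself at time *t–*1, as well as the 7 negative affective experience change indicators".

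The resulting coefficient is described as the effect of "changes in all negative affective experiences on subsequent within-person changes in SI". H1b's prediction step is to be "similar to the procedures used for H1a". Just before this, the general description of dynamic structural equation modeling (DSEM) says that the method can "examine prospective relationships between time *t* predictors and time *t*+1 outcomes".

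**The concern.** The only change indicators the plan defines end at time t, and the SI outcome is also at time t. Both changes span t−1 to t. Table 2 lists the SI and affect items as current-state ratings asked in every survey. Nothing in the equation places SI after affect, although the hypothesis and the interpretation both say that it comes after.

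Controlling for SI at t−1 does not restore the order. It removes carry-over in SI but leaves affect and SI as two ratings made in the same few minutes. A positive coefficient could mean that affect raised SI, that SI raised affect, or that a shared mood or response style moved both. The Strengths and Limitations section itself concedes that associations among self-report measures may reflect shared method variance.

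At stake are the conclusions on H1a and on the predictive part of H1b. The Introduction justifies the study by the scarcity of prospective evidence compared with cross-sectional evidence. The Dissemination Plan intends to use these results to choose intervention targets. A concurrent association reported as precedence would support neither.

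**Working it through.** **Indices side by side** (all from the Data Analysis Plan)

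| Hypothesis | Predictor | Outcome |
|---|---|---|
| H1a as written | affect change ending at t | SI at t |
| H2b | inhibitory control at t | suicide attempt at t+1 |
| H3a | sleep on day d−1 | SI on day d |

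H2b and H3a are lagged explicitly. H1a is not.

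**What the written coefficient estimates.** Let affect follow A(t) = φ·A(t−1) + u(t). Let SI follow S(t) = φ·S(t−1) + β·A(t−1) + v(t), where u and v have unit variance and same-moment correlation ρ. The residualized change in affect is u(t).

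- *As written:* the coefficient of S(t) on u(t), given S(t−1), is cov(u, v)/var(u) = ρ. The lagged effect β does not enter, because u(t) is uncorrelated with A(t−1) and S(t−1). With unit variances, exchanging the two variables also gives ρ when there are no cross-lags.
- *Lagged:* S(t+1) on S(t) and u(t). If β = 0 the coefficient is 0 for any ρ. If ρ = 0 the coefficient is β.

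**How small a ρ suffices.** The power section gives n = 100 and a low-compliance case of 4 × 28 = 112 prompts out of 7 × 28 = 196 (57.1%, as stated there). That is 100 × 112 = 11,200 observations. The standard error is about 1/√11,200 = 0.009, so ρ = 0.1 lies more than ten standard errors from 0. The plan counts any 95% credibility interval that excludes 0 as evidence of an effect.

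**Simulation with seven affect variables.** From the protocol: n = 100 and 112 prompts. Assumed, because the protocol gives no values: autoregression 0.4, correlation 0.6 among the seven affect innovations, and ρ from 0 to 0.5. The lagged effect acts through the mean of the seven. There were 200 replications, and person-mean-centred pooled regression stood in for DSEM. Single and composite columns count positive significant results (nominal 2.5%). The joint column counts at least one two-sided significant result among seven.

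| ρ | β | Written: one affect | Written: composite | Written: joint, any | Lagged: one affect | Lagged: composite |
|---|---|---|---|---|---|---|
| 0 | 0 | 2.5% | 2.0% | 30.5% | 0.5% | 0.0% |
| 0.1 | 0 | 100% | 100% | 98.5% | 3.5% | 2.5% |
| 0.2 | 0 | 100% | 100% | 100% | 3.5% | 4.5% |
| 0.3 | 0 | 100% | 100% | 100% | 1.5% | 1.5% |
| 0.5 | 0 | 100% | 100% | 100% | 2.5% | 7.0% |
| 0 | 0.05 | 3.5% | 4.5% | 30.0% | 93.5% | 98.5% |
| 0 | 0.10 | 2.0% | 1.5% | 27.5% | 100% | 100% |

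The joint column should be read against its chance level, 1 − 0.95⁷ = 30.2%. Per coefficient, the joint written model is significant in 5.3% of cases at ρ = 0, 35.4% at 0.1 and 99.9% at 0.3 (all with β = 0). The mean single-affect coefficients for ρ = 0.1, 0.2, 0.3 and 0.5 are 0.099, 0.199, 0.299 and 0.501, as the algebra predicts. With β = 0, the lagged means are between −0.001 and 0.002.

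**Simulation with one affect variable.** This used 300 runs per correlation, the same n, prompts and autoregression, and β = 0. At ρ = 0.1, 0.2 and 0.4 the written model rejects in 100% of runs, with coefficients of 0.10, 0.20 and 0.40. The lagged model rejects in 5%, 4% and 8%.

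**The case against.** The strongest reply is that the same-time reading is inferred. In the SI regression the change indicators carry no time subscript. The words about preceding and subsequent change, and the general sentence on t to t+1 relationships, suggest that a lag was meant. H2b shows that the authors can write one, so H1a may be only a slip, and the preregistered documents, which are not shown here, may give the right index. This stands as a statement about intent. It does not rescue the text: the only indicators defined end at t and the only outcome is at t, so an analyst who follows the equation fits a concurrent model. If a lag was meant, the paragraph contradicts itself and still needs correcting.

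Three further points stand and narrow the claim:

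- H1b has two parts. The factor analysis concerns co-occurrence, for which same-occasion data are suitable. Only its prediction step is affected.
- A false confirmation needs some same-moment correlation between affect and SI. At ρ = 0 the written model's error is near nominal.
- The autoregression and correlations are assumed, and neither simulation fitted the planned two-level random-slope Bayesian model. Recovering ρ follows from the algebra, so the percentages illustrate the problem and are not the plan's error rates.

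H2 and H3 are not touched by this point.

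**Conclusion.** The concern holds. Read as written, the H1a equation estimates a same-moment association and contains no path from earlier affect to later SI. It errs in both directions. A same-moment correlation of 0.1 alone gives a significant single-affect result in essentially every run at the planned sample size, and a real lagged effect with no same-moment correlation is found no more often than chance would produce.

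The direction of this result rests only on the time indices. The size rests on the protocol's 100 participants and 112 prompts, and on the assumed autoregression and correlations. The conclusions affected are H1a and the prediction part of H1b. The text must be corrected before analysis, whether the cause is a slip or a deliberate choice.

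**What to change.** State the indices explicitly for H1a and for H1b's prediction step: SI at t+1 regressed on SI at t and on affect at t, entered either as residualized change or as the within-person deviation. This matches the lag structure already written for H2b. Report the same-occasion association separately and label it concurrent.

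The change is one line in the model specification and needs no new data, since analysis starts only after data collection ends.

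The cost is that lagged effects are usually smaller than concurrent ones, and entering seven correlated predictors together dilutes them further. In the simulation, the joint lagged model found each coefficient significant in only 9.1% of cases at a total lagged effect of 0.05, and 17.1% at 0.10, while single-affect and composite models found the effect in 93.5% to 100% of runs. The revised text should therefore say whether H1a's claim about each experience individually will be judged from separate models or from the joint one.
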